### 11.3 Data Review

A review of the data is anticipated through the data review process led by Data Management before database lock.

## 12 Statistical Methods and Determination of Sample Size

### 12.1 Statistical Methods

The statistical analyses will be carried out under the responsibility of the SP's Biostatistics platform, with the SAS® software, version 9.4 or above (SAS Institute, Cary, NC, USA). SAEs will be managed by the Sponsor's PV department. A detailed statistical analysis plan (SAP) will be written and validated before the database lock. In accordance with the protocol, the SAP will describe all the analyses to be performed, statistical tables and listings including descriptions of the analysis conventions to be used.

#### 12.1.1 Hypotheses and Statistical Methods for Primary Objective(s)

##### 12.1.1.1 Hypotheses

The primary objective is to demonstrate non-inferiority of investigational SHAN 5® compared to licensed SHAN 5® at D84, ie, 28 days after the third vaccine injection on Hep B and Pertussis immunogenicity responses, based on the following hypotheses:

For Hepatitis B:

- $H_0: P_{\text{ISHAN 5}} - P_{\text{CSHAN 5}} \leq -10\%$
- $H_1: P_{\text{ISHAN 5}} - P_{\text{CSHAN 5}} > -10\%$

With P = proportion of subjects with an anti-HBs Ab concentration  $\geq 10$  mIU/mL at D84 (%).

For Pertussis (on PT and FIM):

- $H_0: aGMC_{iSHAN\ 5} / aGMC_{cSHAN\ 5} \leq 1/2$
- $H_1: aGMC_{iSHAN\ 5} / aGMC_{cSHAN\ 5} > 1/2$

#### 12.1.1.2 Statistical Methods

For HepB, non-inferiority testing will be based on the use of the two-sided 95% confidence interval (CI) of the difference of proportions of subjects with an anti-HBs Ab concentration  $\geq 10$  mIU/mL at D84. The 95% CI for differences will be calculated using Wilson score method without continuity correction.

Hepatitis B non-inferiority will be demonstrated if the lower limit of the 95% CI of the difference of the two proportions  $P_{iSHAN\ 5} - P_{cSHAN\ 5}$  is  $> -10\%$ , meaning that the null hypothesis  $H_0$  is rejected.

For Pertussis, non-inferiority testing will be based on the use of aGMCs and their 95%CI, on both PT and FIM results.

Adjusted GMCs will be computed using analysis of covariance to adjust for baseline disparities and consider the correlation between pre- and post-vaccination concentration (log-transformed), through an ANCOVA model using the pre-vaccination (D0) concentration as a covariate for adjustment in order to account for the associated variability. The 95% CI of ratio between aGMCs will be calculated using normal approximation of the log10 of the concentration.

Pertussis on-inferiority will be demonstrated if the lower limits of the 95% CI of the ratio of adjusted GMCs for PT and for FIM antigens are  $> 0.5$ .

Overall non-inferiority will be demonstrated if the Pertussis (PT and FIM) and Hepatitis B non-inferiority are demonstrated.

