### 3 Investigators and Study Organization

This study will be conducted in approximately 8 centers in India. This is a multi-center study with multiple investigators. Details of the study centers, and the Investigators at each center are provided in the “List of Investigators and Centers Involved in the Trial” document.

An internal safety management team (SMT) will perform an analysis of safety data during the conduct of the study.

The Sponsor’s Responsible medical officer (the person authorized to sign this protocol and any amendments on behalf of Sponsor) is [REDACTED] Clinical Team Leader.

Apart from this the Investigators involved in this trial across various sites will also sign in signature page of the protocol, mentioning that they have gone through as well as understand this protocol and ready to conduct this trial according to the protocol, Good Clinical Practice and applicable local regulatory requirements.

The Sponsor will provide clinical trial supplies (vaccines and other study material).The monitoring of the clinical trial will be done by the Shantha’s Clinical Operations department.

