## 6.5 Randomization and Allocation Procedures

After taking consent from the parent/LAR, the investigator will allot screening numbera to each subject. The screening number will be an alpha-numerical consisting of 3-digit center identifier, 3-digit subject identifier and "SC" at the end. The 3-digit center identifier will be assigned to specific sites, before start of the trial. The 3-digit subject identifier corresponds to the chronological order of screening in the center (e.g., the 21st subject screened in center 1 will be allotted with a screening number: 001-021-SC).

After collection of first blood sample (BL1) at V01, the investigator will allocate an inclusion / enrollment number to each subject. The enrollment number will be a 6 digits string with a 3-digit center identifier, 3-digit subject identifier. As mentioned earlier, the 3-digit center identifier will be assigned to specific sites, before start of the trial. The 3-digit subject identifier corresponds to the chronological order of enrollment in the center and the Randomization number (e.g., the 21st subject included in center 1 will be subject: 001-021). Once the subject is enrolled, the enrollment number will remain the same in Stage 1 and Stage 2 i.e. subject with number 001-021 in Stage 1 will continue with the same number 001-021 in Stage 2 also.

Scratchable randomization list required for Stage 1 will be prepared by Sanofi Pasteur Biostatistics platform. The list will be created with a 1:1 ratio (iSHAN5 : cSHAN 5) using permuted blocks and will be stratified by center. Each subject enrollment number will correspond to one entry on the randomization sheet. At the end, the randomization sheet will contain information stating the name of the vaccine(s) (covered by a silver colored patch) allocated to the particular subject number, space for signature and date. Each entry in the randomization sheet will be signed and dated by the Investigator or the designee.. Each subject will be vaccinated with the product(s) corresponding to the group mentioned on the randomization list. If the dose initially taken for the vaccination is broken or cannot be used, the Investigator will take another dose of the same vaccine.

---

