## 12.5 Determination of Sample Size and Power Calculation

A total of 460 subjects will be enrolled in the study. Subjects will be randomly allocated to one of the two groups (iSHAN 5 or cSHAN 5) using the 1:1 ratio.

The sample size is calculated based on primary study objectives, with an alpha level of 2.5% (one-sided hypotheses), a 10% non-inferiority clinical margin for the hepatitis B responses, a 2-fold ratio for aGMC ratio for pertussis responses (PT and FIM) and an assumption of 85% of enrolled subjects fulfilling the Per Protocol definitions in each group.

The sample size calculations are based on the following assumptions:

| Endpoints | Ref std(log10) seroprotection rate* or | ratio or $\delta$ for NI | With unilateral alpha 0.025 |
|-----------|----------------------------------------|--------------------------|-----------------------------|
|           |                                        |                          | Power for NI                |

|                             |                  |     |              |
|-----------------------------|------------------|-----|--------------|
|                             |                  |     | N=390 |
| Pertussis anti-PT    | log sd aGMC=0,75 | 2   | 97,7%        |
| Pertussis anti-FIM   | log sd aGMC=0,85 | 2   | 93,7%        |
| Anti-HBs ≥ 10 mIU/ml | 95%              | 10% | 98,4%        |
| Overall power        |                  |     | 90,1%        |

\* reference level were observed on previous study samples results.

Based on simulations, testing the null hypothesis on Pertussis responses with a power of 91.5% (on aGMCs at Day 84), and assuming observed standard deviations of  $\log_{10}(\text{aGMCs})$  of 0.75 and 0.85, respectively on PT and FIM results, will require a total of 195 evaluable subjects in each group. With such a sample size and an assumption of 95% of subjects with an anti-HBs Ab concentration  $\geq 10$  mIU/mL at D84, the power to demonstrate non-inferiority on HepB will be 98.4% (using the Farrington and Manning method) meaning that the overall power of the trial is at least 90%.

Considering a 15% of subjects non-evaluable at D84, a total of 460 subjects should be included in the trial to reach the primary objective with an overall power of at least 90%.

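### Randomisation is stratified by centre but the primary PT and FIM model does not name centre; if centre predicts response, a small gain in precision is forgone

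*Protocol*

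**What the plan says.** Section 6.5 of the protocol has the list drawn up 1:1, "using permuted blocks and will be stratified by center". Section 3 gives the scale: "This study will be conducted in approximately 8 centers in India".

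Section 12.1.1.2 then fixes the primary methods. For anti-PT and anti-FIM, the adjusted GMCs are obtained "through an ANCOVA model using the pre-vaccination (D0) concentration as a covariate for adjustment in order to account for the associated variability". D0 concentration is the only covariate named. For hepatitis B, "The 95% CI for differences will be calculated using Wilson score method without continuity correction", with no mention of strata. The Statistical Methods part of the synopsis repeats both.

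Section 12.5 gives the power at 195 evaluable subjects per group, one-sided alpha 2.5%: 97.7% for anti-PT, 93.7% for anti-FIM, 98.4% for hepatitis B and 90.1% overall. Section 12.1 says that an SAP will be written in accordance with the protocol; it is not at hand.

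**The concern.** Permuted blocks within centre keep the two groups balanced on centre, so differences between centres largely cancel out of the comparison of vaccines. A model without centre still leaves those differences in its residual variance. If centres differ in response, the standard error then overstates the true variability of the contrast. The interval is too wide and the test runs below its nominal error rate.

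Pertussis precision matters here. All three tests must succeed, overall power is 90.1% against a target of at least 90%, and anti-FIM has the lowest power of the three. Section 1.2 reports that two previous trials of this product narrowly missed their pertussis criteria, one for lot consistency and one for non-inferiority. Section 5.1.2 wants sites in various parts of India, which makes some difference between centres plausible, although no figure is given.

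**Working it through.** **Inputs.** From section 12.5: n = 195 per group; margin a ratio of 1/2, so log10(2) = 0.3010; SD of log10 0.75 for PT ("log sd aGMC=0,75") and 0.85 for FIM; one-sided alpha 0.025; hepatitis B 95% in both groups with a margin of 10 points. From section 3: about 8 centres. Assumed, because the documents do not give it: f, the share of residual log10 variance that centre explains, taken as 0, 5, 10 and 20%.

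**The plan's own figures.** The standard error is SD × √(2/195).

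- FIM: 0.85 × 0.10127 = 0.08608, and 0.3010/0.08608 = 3.497. The noncentral t with 388 df gives 93.7%.
- PT: 0.75 × 0.10127 = 0.07596, and 0.3010/0.07596 = 3.963. Power 97.7%.
- Hepatitis B, Farrington-Manning: 98.4%.
- Overall: 0.977 × 0.937 × 0.984 = 90.1%.
- Enrolment: 390/0.85 = 459, against 460 planned.

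Every stated figure reproduces without a centre term.

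**Anti-FIM with and without centre.** Under stratified allocation, the contrast varies with SD × √(1 − f) in both analyses. They differ only in the standard error used to judge it. With critical value 1.966:

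- without centre: power ≈ Φ[(3.497 − 1.966)/√(1 − f)]
- with centre: power ≈ Φ[3.497/√(1 − f) − 1.966]
- one-sided error without centre ≈ Φ[−1.966/√(1 − f)]

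A simulation serves as a check: 8 centres, blocks of 4 (assumed), 390 subjects, SD 0.85 taken as the residual SD, 6,000 runs per setting. Its simulation error is about 0.3 points for power and 0.2 points for the error rate.

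| f | Power without → with centre, formula | Same, simulated | One-sided error without centre, formula / simulated | Narrowing of interval, 1 − √(1 − f) |
|---|---|---|---|---|
| 0 | 93.7 → 93.7% | 93.3 → 93.2% | 2.5 / 2.4% | 0% |
| 5% | 94.2 → 94.8% | 93.9 → 94.5% | 2.2 / 2.3% | 2.5% |
| 10% | 94.7 → 95.7% | 94.5 → 95.6% | 1.9 / 2.2% | 5.1% |
| 20% | 95.7 → 97.4% | 95.8 → 97.4% | 1.4 / 1.3% | 10.6% |

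The gain for FIM is about 0.6, 1 and 1.6 to 1.7 points at f = 5, 10 and 20%. For PT the same formulas, with 3.963 in place of 3.497, give about 0.2, 0.4 and 0.6 points. With centre in the model the simulated error was 2.4, 2.6, 2.8 and 2.2%, scatter around 2.5% that simulation error can explain.

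**Price of the term.** Eight centres use 7 degrees of freedom, from 387 to 380. At f = 0 the simulated power is the same within error.

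**Hepatitis B.** At 95% seroprotection, 0.05 × 195 = 9.75 non-responders are expected per group, or 9.75/8 ≈ 1.2 per group and centre. Exact power with the planned interval is 98.9%. There is little to recover.

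**The case against.** The strongest case against is that nothing in the plan is wrong. The powers are right for the stated analysis, the target of at least 90% is met, and the omission errs on the conservative side. All of that stands, and it limits the point to efficiency.

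The size also rests on a number that the documents do not contain. The SDs of 0.75 and 0.85 do not settle it, because a large SD says nothing about the share due to centre, and section 12.5 does not say whether these SDs are total or within-centre. Differences between centres in maternal antibody are at least partly captured by the infant's D0 concentration, which is already in the model. Only what remains after D0 counts. This stands too, so the size can be given only as a range that starts at zero.

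It can further be said that the model's remaining terms belong in the SAP, and that naming D0 does not exclude centre. This has less weight. Section 12.1.1.2 names the model, the covariate and the interval for the primary endpoints, and the SAP is to accord with the protocol. An SAP that follows the text as written would leave centre out.

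Three stronger readings are tempting, and the documents do not support them:

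- **That planned anti-FIM power is lost, or that the sample size is wrong.** The 93.7% already describes an analysis without centre.
- **That the gain is the distance from 93.7% to the adjusted power, 2 points at f = 10%.** When centre matters, stratified allocation raises the power of the unadjusted analysis as well (94.7% by formula), so the gain is about half that.
- **That the primary hepatitis B interval should be stratified.** With about 1.2 expected non-responders per group and centre, the gain is negligible, and the change would bring in further choices of interval and pooling.

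**Conclusion.** The point holds as a modest mismatch between design and analysis. Randomisation is stratified by centre, and the primary PT and FIM model as written does not use centre. If centre predicts the D84 response after D0 adjustment, the intervals are wider than needed and the one-sided error falls below 2.5%. Validity is not threatened: the omission does not raise the risk of a false claim of non-inferiority.

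For anti-FIM the forgone power is zero if centre explains nothing, and about 0.6, 1 and 1.6 points if it explains 5, 10 or 20% of residual variance. These shares are assumed, as are 8 centres of nearly equal size and blocks of 4. The direction is certain wherever centre matters; the size cannot be found from the documents. Because the term costs almost nothing and overall power has little reserve above 90%, the change is worth making.

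**What to change.** In section 12.1.1.2 and in the synopsis, state the primary model for anti-PT and anti-FIM as log10(D84) = vaccine group + log10(D0) + centre. Take centre as a fixed effect, pool small centres by a rule set before unblinding, and take the aGMC ratio and its 95% CI from this model. Keep the model without centre as a sensitivity analysis. If the sponsor prefers to omit centre, give the reason in the same place.

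Leave the Wilson interval as the primary hepatitis B analysis; a centre-stratified difference is at most a sensitivity analysis.

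The cost is a sentence or two in each place and about 7 degrees of freedom. It needs no further data or subjects, and the sample size and power table can stand.

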### 12.1.2 Hypotheses and Statistical Methods for Secondary Objective(s)

#### 12.1.2.1 Hypotheses

All analyses will be descriptive; no hypotheses will be tested.

#### 12.1.2.2 Statistical Methods

Descriptive statistics will be produced for each secondary endpoint.

The main safety and immunogenicity parameters will be described with 95% CI.

Immunogenicity endpoints will be summarized by vaccine group and by time-point (pre and post primary series vaccination and pre and post booster vaccination).

The following parameters will be used for anti-D, anti-T, anti-Hep B, anti- Pertussis and anti-Hib antibody concentration:

- Percentage of subjects with concentration above predefined cut-off (as per secondary endpoints)
- Percentage of subjects with  $\geq 4$  fold rise in anti-pertussis antibody concentration and / or vaccine response
- Geometric mean ratio (GMCR) of individual Ab concentration
- GMC for each valence, adjusted GMCs for PT, FIM, PRN and FHA

For descriptive immunogenicity analyses, geometric mean concentrations (GMCs), adjusted GMCs (for Pertussis endpoints) and geometric mean concentration ratio (GMCR) will be calculated with their 95% CI (normal approximation method).

Reverse Cumulative Distribution Curves (RCDCs) of individual concentration will be presented for the two groups.

For descriptive safety analyses, percentages will be presented with their 95% CI (Clopper-Pearson method).

## 12.2 Analysis Sets

### 12.2.1 Full Analysis Set

The full analysis set (FAS) is defined for each stage of the trial as the subset of enrolled subjects who received at least 1 dose of the study vaccine as defined in the corresponding stage.

### 12.2.2 Safety Analysis Set

The safety analysis set (SafAS) is defined for each stage of the trial as those subjects who have received at least 1 dose of the study vaccinea as defined in the corresponding stage. All subjects will have their safety analyzed after each dose according to the vaccine they actually received and after any dose according to the vaccine received at the first dose (for Stage 1) and after the booster dose overall.

Safety data recorded for a vaccine received out of the protocol design will be excluded from the analysis (and listed separately).

The analysis will be based upon the number of subjects for whom each safety assessment was performed. The number of subjects used to analyze safety measurements may therefore differ between the various safety assessments.

---

a for which safety data are scheduled to be collected

### 12.2.3 Per-Protocol Analysis Set

The per-protocol analysis set (PPAS) is a subset of the FAS and is defined for Stage 1 only. The subjects presenting with at least one of the following relevant protocol deviations will be excluded from the PPAS:

- Subject did not meet all protocol-specified inclusion criteria or met at least one of the protocol-specified exclusion criteria
- Subject did not complete the vaccination schedule
- Subject received a vaccine other than the one that he / she was randomized to receive
- Preparation and / or administration of vaccine was not done as per-protocol
- Subject did not receive vaccine in the proper time window:
  - Vaccination 2 outside the 28-35 days range since vaccination 1
  - Vaccination 3 outside the 28-35 days range since vaccination 2
- Subject did not provide a post-dose serology sample at V04 in the proper time window (outside 28-35 days range since vaccination 3) or a post-dose serology sample was not drawn
- Subject's serology sample at V04 did not produce a valid test result for Hep B.
- Subject's serology samples at V01 or V04 did not produce a valid test result for PT or FIM.
- Subject received a protocol-prohibited therapy / medication / vaccine (from Categories 2 and 3 as defined in Section 6.7)

In addition to the reasons listed above, subjects will also be excluded from the PPAS if their serology sample did not produce a valid test result (i.e., results for all antigens are missing).

In the event of a local or national immunization program e.g. with national immunization with polio vaccine, subjects who receive one or more doses of such vaccine at any time during the trial will not be withdrawn from the trial. If the Home Visit/OPD Visit (HV/OPDV) happens later than 9th day, Protocol deviation will not be filed and the same will be documented in the medical chart.

This list may not be exhaustive. The above protocol deviations leading to exclusion from the PPAS may be detailed and completed in the Statistical Analysis Plan (SAP) following a data review (if necessary). The PPAS definition will be finalized before the database lock.

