Anti-hepatitis B antibodies will be measured by the commercially available VITROS ECi/ECiQ Immunodiagnostic System using chemiluminescence detection technology. The VITROS ECi Immunodiagnostic system uses an antibody mediated antigen sandwich formation to detect the presence of anti-HBsAg total immunoglobulin in human serum. This involves the reaction of anti-HBsAg in the sample with plasma-derived HBsAg (ad and ay subtypes) coated onto the wells. A horseradish peroxidase (HRP)-labeled HBsAg conjugate (ad and ay subtypes) then complexes with the bound anti-HBs, forming an antigen sandwich. Substrate is then added which catalyzes HRP, producing light. The light signals are read by the VITROS ECi/ECiQ Immunodiagnostic System and the amount of HRP conjugate bound is directly proportional to the concentration of anti-HBs antibodies present in the sample. Results are reported in mIU/mL by comparison to a calibrator provided by the manufacturer that was previously calibrated to the WHO First International Reference Preparation for Antibody to HBsAg (1977).

Serum levels of anti-*Haemophilus influenzae* type b (Hib) PRP antibodies are determined by RIA, in which serum samples are incubated with radiolabeled PRP. Specific antibodies bind to antigen labeled with titrated capsular polysaccharide (H-PRP) to form antigen-antibody complexes. These complexes are precipitated with ammonium sulfate and collected by centrifugation. The radioactivity measured in the precipitated pellet, in counts per minute (CPM), is proportional to the

amount of anti-PRP antibody present in the serum sample. The concentration of anti-PRP antibody in the serum sample is determined from the concentration response curve generated by the titration results of dilutions of the reference standard analyzed in the assay. Results will be reported in micrograms (µg)/mL by comparison to Center for Biologics Evaluation and Research (CBER), Lot No. 1983 reference standard. The LLOQ for the anti-PRP assay was 0.06 µg/mL. Samples calculated to a value less than 0.06 were reported as <0.06 µg/mL.

All the assays will be set up and validated at the laboratory prior to running the clinical samples.

In case of insufficient sample volume, the priority of assays for testing is as follows:

1. MSD-ECL for anti-PT, FHA, PRN, FIM, Dip and Tet
2. Vitros-ECi for anti-Hepatitis B
3. RIA for anti-PRP

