### 12.2.4 Populations Used in Analyses

The primary immunogenicity analyses (non-inferiority testing on Stage 1) will be performed on the PPAS analysis set, and will be confirmed on the FAS. The secondary immunogenicity descriptive analyses for Stage 1 will also be performed on PPAS and FAS. In the FAS, for stage1, subjects will be analyzed by the vaccine group to which they were randomized.

For stage 2, the immunogenicity will be performed on the FAS and described overall and according to the randomized vaccine group at Stage 1.

The safety analysis will be performed on the SafAS. Subjects will be analyzed according to the vaccine they actually received at the corresponding Stage.

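### The per-protocol set applies its assay-validity criteria to the whole infant, so a missing result on one primary antigen removes valid results on the others from the main analysis

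*Protocol*

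**What the plan says.** Section 12.2.3 sets up a single PPAS for Stage 1 and removes whole subjects: "The subjects presenting with at least one of the following relevant protocol deviations will be excluded from the PPAS". Two of the listed deviations concern laboratory results rather than conduct. One is the lack of a usable hepatitis B measurement from the V04 blood draw. The other covers the two pertussis antigens and both visits: "Subject's serology samples at V01 or V04 did not produce a valid test result for PT or FIM".

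A closing sentence adds that subjects are also "excluded from the PPAS if their serology sample did not produce a valid test result (i.e., results for all antigens are missing").

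Section 12.2.4 says that the primary non-inferiority analyses "will be performed on the PPAS analysis set, and will be confirmed on the FAS". It also says: "The secondary immunogenicity descriptive analyses for Stage 1 will also be performed on PPAS and FAS".

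Section 9.2.2.2 anticipates short serum: "In case of insufficient sample volume, the priority of assays for testing is as follows". The multiplexed MSD-ECL assay (PT, FHA, PRN, FIM, diphtheria, tetanus) comes first, hepatitis B second and anti-PRP third.

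Section 12.1.1.2 bases the hepatitis B test on D84 proportions alone. PT and FIM are each compared by ANCOVA with the D0 concentration as covariate.

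**The concern.** The validity bullets ask for more than each test needs. The hepatitis B comparison needs one number per infant, the V04 anti-HBs, yet an infant who has it is excluded when the V01 PT or FIM result is invalid. The PT and FIM comparisons need V01 and V04 values of their own antigen, yet an infant who has both is excluded when hepatitis B was not measured at V04.

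The second case is the one that the assay ranking makes likely. If V04 serum runs out after the first-priority assay, PT and FIM are obtained and hepatitis B is not. The PPAS then excludes the PT and FIM results because the second-priority assay was not run. Valid diphtheria, tetanus, FHA, PRN and PRP results leave the secondary PPAS summaries in the same way.

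At stake is precision in the main analysis of three tests that must all succeed, in a plan whose overall power is 90.1% against a target of at least 90%.

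**Working it through.** **Which result each test uses, and what the PPAS demands**

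| Test | Results used (12.1.1.2) | Results required for the PPAS (12.2.3) |
|---|---|---|
| Hepatitis B | V04 anti-HBs | V04 anti-HBs, plus V01 and V04 PT and FIM |
| PT | V01 and V04 anti-PT | the same full list |
| FIM | V01 and V04 anti-FIM | the same full list |

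**Inputs (section 12.5).** 195 evaluable per group; one-sided alpha 0.025; pertussis margin a 2-fold ratio, so log10(2) = 0.301; SD of log10 concentration 0.75 (PT) and 0.85 (FIM); hepatitis B seroprotection 95%, taken here in both groups, with a margin of 10 points; 15% non-evaluable.

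**Reproducing the plan's figures at 195 per group**

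- PT: Φ(0.301 / (0.75 × √(2/195)) − 1.96) = Φ(2.00) = 97.7% (stated 97.7%).
- FIM: Φ(0.301 / (0.85 × √(2/195)) − 1.96) = Φ(1.54) = 93.8% (stated 93.7%, which the noncentral t gives exactly).
- Hepatitis B, Farrington-Manning: the restricted null proportions are 0.870 and 0.970, so SE0 = √((0.870 × 0.130 + 0.970 × 0.030)/195) = 0.0270. SE1 = √(2 × 0.95 × 0.05/195) = 0.0221. Power = Φ((0.10 − 1.96 × 0.0270)/0.0221) = 98.4% (stated 98.4%).
- Overall, as the product of the three: 90.2% (stated 90.1%).
- Enrolment: 390/0.85 = 458.8, so 459 (stated 460).

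The plan's figures are right and are not in dispute.

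**Extra loss beyond the allowance.** The protocol gives no invalid-result rate, so 2%, 5% and 10% are assumptions. Rounded down, 195 × 0.98, 195 × 0.95 and 195 × 0.90 give 191, 185 and 175 per group.

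*Case A: the extra infants lack only V04 hepatitis B.* As written, all three tests fall to the reduced n. With endpoint-specific criteria, PT and FIM stay at 195 and only hepatitis B falls.

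| Extra loss | n per group | PT | FIM | Hep B | Overall as written | Overall, endpoint-specific | Gain (points, unrounded) |
|---|---|---|---|---|---|---|---|
| 2% | 191 | 97.5% | 93.3% | 98.2% | 89.3% | 90.0% | 0.6 |
| 5% | 185 | 97.1% | 92.6% | 97.8% | 88.0% | 89.7% | 1.7 |
| 10% | 175 | 96.4% | 91.2% | 97.1% | 85.3% | 89.0% | 3.7 |

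The PT, FIM and Hep B columns are as written, at the reduced n.

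*Case B: the extra infants have valid V04 hepatitis B but no valid PT and FIM pair.* Here only hepatitis B can be kept at 195. Overall power is 89.3%, 88.0% and 85.3% as written, against 89.5%, 88.5% and 86.4%. The gains are 0.2, 0.5 and 1.1 points.

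Case B gains less because an infant without a valid baseline FIM cannot enter the FIM ANCOVA under either rule, and likewise for PT. Both antigens come from one multiplexed assay, so short volume will usually remove both.

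**The case against.** Four points against the concern carry weight.

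- **The data are not lost to the trial.** A reader might infer that these infants vanish from every analysis. They do not: the FAS (12.2.1) requires only one dose and has no serology criterion, and both the primary and the secondary Stage 1 immunogenicity analyses are also run on it. This stands. The cost falls on the main analysis only.
- **The losses may already be budgeted.** Section 12.5 assumes that 85% of enrolled subjects meet the per-protocol definitions, which include these bullets, so 195 per group is a count after exclusions. A reader might infer that the trial is underpowered. Nothing in the protocol shows that 15% is too small, so no shortfall is demonstrated. This stands too.
- **One common set suits a joint conclusion.** Success requires hepatitis B, PT and FIM together, so a single complete-data population is defensible. But each test is valid on its own evaluable infants, and requiring all three to pass does not require a shared denominator.
- **The SAP may refine the PPAS.** Section 12.2.3 allows the list to be detailed and completed before database lock, and the SAP was not available for this review. The two bullets are nevertheless already fixed as subject-level exclusions.

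Two further readings are tempting and not supported. The sentence on all antigens missing might seem to contradict the bullets. It is worded as an addition to them, and any sample that it describes already meets a bullet, so it is redundant. One might also suppose that short or failed samples concentrate in small or preterm infants and bias the result. Preterm infants are eligible, but the protocol says nothing about who yields short samples. Allocation is randomized and laboratory staff are blinded, so no mechanism for a difference between groups is shown.

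**Conclusion.** The point holds as one of efficiency. As written, the main analysis excludes valid primary results for reasons unrelated to the endpoint being tested, and it does so in the very case that the assay ranking foresees. That the ranking is meant to protect the pertussis results is an inference, since the protocol states no purpose for it.

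The size is modest and rests on assumed rates. With 2% to 10% of infants lacking only V04 hepatitis B on top of the 15% allowance, endpoint-specific criteria recover about 0.6 to 3.7 points of overall power. If only PT and FIM are invalid, they recover about 0.2 to 1.1 points. If all such losses sit inside the allowance, the stated 90.1% stands. The calculation multiplies the three powers, which reproduces the plan's overall figure. No bias and no invalid test is shown. Low severity.

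**What to change.** In section 12.2.3, keep the eligibility, vaccination, timing and prohibited-therapy exclusions common to all endpoints, and replace the two validity bullets with criteria per endpoint:

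- hepatitis B: a valid V04 anti-HBs result;
- PT: valid V01 and V04 anti-PT results;
- FIM: valid V01 and V04 anti-FIM results;
- each other antigen: its own valid result.

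The sentence on all antigens missing can stay as the common minimum, a role it would actually have once the bullets are endpoint-specific.

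The cost is a rewording before database lock, with no change to conduct, sample size, margins or alpha. The one downside is that denominators will differ slightly between endpoints, so tables should show the number analysed for each.
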